### Ethics, clinical registries, potential conflicts of interest

The trial will be conducted in accordance with the Declaration of Helsinki. The trial protocol was approved by the Biomedical Ethics Committee of West China Hospital, Sichuan University (ethics reference: 2022 (1070)).

The study was registered on the Chinese Registry website (registered in ChiCTR.org with the identifier ChiCTR2200064175).

The authors declare no conflicts of interest.

### Randomization

After the baseline measurement, the computer software SPSS (26.0) will be used to generate a random number table, and patients will be assigned to the CT or the DT in a ratio of 1:1 by a simple random method. Write the random number assigned to each group on a piece of paper and place it in an opaque envelope. Envelopes will be randomly assigned to participants by the independent individual not involved in the study.

### Blinding

This trial is single-blinded. Patients could not be blinded due to the treatment method, but each patient would only know their trial protocol at randomization. Before the start of the trial, standardized training will be given to the researchers. After grouping, an independent person will inform the researchers of the grouping, and the researchers only know the patients in this group. Evaluators, statisticians and data managers will be blinded during the trial.

### Withdrawal and adverse events

Each group has the possibility of patients dropping out of the trial. The researcher needs to record the information about the trial withdrawal, including the reason and time of withdrawal. At the same time, the researchers will record the adverse events that occurs during the trial in the CRF form, including the type, frequency, treatment measures and results of the adverse events. The adverse events will be adjudicated by three rehabilitation physicians.

## Statistical analysis

Data analysis will use an intention-to-treat analysis strategy. Data analyses will use SPSS (26.0). P ≤ 0.05 will be significantly different. The raw data collected by fNIRS will be preprocessed by NIRSPARK software, including artifact processing, filtering, segmentation and baseline comparison. At the same time, the fNIRS data will be analyzed using the statistical analysis module of MATLAB (R2020a). Component comparability of baseline data between the two groups will be performed using the chi-square test and independent samples t test. The frequency and percentage of count data will be calculated in the statistical description; the data of measurement data following a normal distribution will be described by the mean ± standard deviation. For the comparison between groups after the intervention, the independent samples t test will be used if the data follow a normal distribution, and the Mann‒Whitney U rank sum test will be used if the data are nonnormally distributed. For intragroup comparisons before and after the intervention, a paired t test will be used if the data follow a normal distribution, and the Wilcoxon rank sum test will be used for data that are not normally distributed.

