### Primary outcomes:

(1) The difference in knee pain before and after treatment, will be measured by the NRS, a standard tool for the study of chronic pain, that is an 11-number scale from 0 to 10, with 0 being no pain and 10 being severe pain. The minimum clinically important difference (MICD) is 1.8 [32, 33].(2) Association of pain severity with task-activated fNIRS. Data collection: The NirSmart portable near-infrared functional brain imaging system (Danyang Huichuang Medical Equipment Co., Ltd., China) will collect the cerebral cortical activity of the participants in the 30-s chair-stand test, the timed up-and-go test, the 40-m fast-paced walk test and the stair-climb test (9 steps) [34]. The test will be carried out in a quiet corridor and stairwell. Before each test, the test procedure will be explained to the participants, and the participants will be informed that if there is no special situation to keep quiet during the test, the test will be started after the participants fully understand. At the beginning of each test, the participants will need to stand quietly for 10 s to obtain the resting state fNIRS, and then the corresponding test will be carried out according to the rules. Forty effective test channels consisting of 24 light transmitters and 16 light receivers cover the functional areas of the whole brain. Changes in blood oxygen will be measured at two wavelengths (760 and 850 nm) with a sampling frequency of 10 Hz.

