### Sample size

The sample size will be determined by comparing the NRS scores before and after treatment based on a preliminary study of the first 10 participants. With a yielding power of 90% and a significance level of 0.05, using G*Power (3.1.9.4) software, the sample size is intended to consist of 30 participants in each group. With a 20% dropout rate, the two groups required 72 participants. KOA patients and healthy volunteers will be calculated in a ratio of 3:1, for a total of 24 healthy volunteers.

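### Two primary outcomes share one unadjusted 5% level, with no hierarchy or success rule and no confirmatory visit, task or region for the fNIRS primary

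*Protocol article*

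**What the plan says.** The Primary outcomes section of the protocol article names two primaries. The first is pain: "The difference in knee pain before and after treatment, will be measured by the NRS". The second is "Association of pain severity with task-activated fNIRS". The second is recorded "in the 30-s chair-stand test, the timed up-and-go test, the 40-m fast-paced walk test and the stair-climb test (9 steps"), and the same item says that "Forty effective test channels consisting of 24 light transmitters and 16 light receivers cover the functional areas of the whole brain". The Outcome measures section gives a baseline and two later measurements, T5 and T10.

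The Statistical analysis section states one threshold, "P ≤ 0.05 will be significantly different". It gives t tests or rank tests for comparisons between and within groups. For fNIRS it names the preprocessing software and a MATLAB statistics module.

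The Sample size section rests on NRS alone, with a "yielding power of 90% and a significance level of 0.05". That 0.05 is not divided between the two primaries.

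The text shown gives no order of testing, no alpha split, no rule on whether one or both primaries must succeed, and no designated visit, task or region for the fNIRS primary. Table 1, the participant timeline, is not reproduced in the copy reviewed.

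**The concern.** A trial with two primaries needs a rule that says what counts as success. If either may carry the claim and each is tested at 0.05, the chance of at least one false claim exceeds 5%. The fNIRS primary adds to this because, as described, it is not a single variable: it is collected in four tasks, over many channels and at two post-baseline visits. Whoever analyses the data can choose among these after seeing them.

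The stakes are in the article's own aims. It intends to decide whether fNIRS can serve as an indicator of pain severity, and its Conclusion looks ahead to an objective clinical index. A claim of that kind should rest on a measure fixed in advance, at a known error rate.

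**Working it through.** **Inputs from the article.** Threshold 0.05 (Statistical analysis); 2 primaries, 4 tasks, 40 channels (Primary outcomes); 2 post-baseline visits (Outcome measures); 30 per group, 90% power, significance level 0.05 (Sample size).

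**Assumptions.** Tests are two-sided, since sidedness is not stated. All null hypotheses are true. Test statistics are normal with a common pairwise correlation ρ. The article gives no value for ρ, so a range is shown.

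**Plan's own figure.** The article reports no familywise error rate, so there is none to reproduce. The 30 per group cannot be reproduced either, because no effect size or SD is given. Under a two-sided two-sample t test, 30 per group with 90% power implies a standardised difference of 0.85.

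**Formulas.** With m independent tests, P(at least one false positive) = 1 − 0.95^m. With common correlation ρ, it is 1 − E{[Φ((1.96 − √ρ·Z)/√(1 − ρ)) − Φ((−1.96 − √ρ·Z)/√(1 − ρ))]^m}, where Z is standard normal, evaluated by numerical integration.

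**Step 1: two primaries, either sufficing (m = 2).**
- ρ = 0: 1 − 0.95² = 9.75%
- ρ = 0.7: about 8.3%

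**Step 2: one fNIRS summary per task at each visit, no channel-wise testing (m = 4 × 2 = 8).**
- ρ = 0: 1 − 0.95⁸ = 33.7%
- ρ = 0.5: 25%
- ρ = 0.7: 19%
- ρ = 0.9: 12%

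**Step 3: conditional case, every channel tested singly in every task at one visit (m = 40 × 4 = 160).** The article does not state this analysis.
- Expected false positives: 160 × 0.05 = 8, whatever the correlation
- ρ = 0: 1 − 0.95¹⁶⁰ = 99.97%
- ρ = 0.3: 98.5%
- ρ = 0.5: 87%
- ρ = 0.7: 56%
- ρ = 0.8: 40%
- ρ = 0.9: 24%

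**Step 4: what the remedies cost the NRS test.** Take the implied standardised difference of 0.85 and 30 per group.
- Fixed sequence with NRS first: NRS is tested at 0.05 and power stays at 90%.
- Equal split, 0.05/2 = 0.025 each: power falls to 83.7%, and 36 per group before dropout would be needed to restore 90%.

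**The case against.** The strongest reply is that the channel and task counts describe data collection, not the unit of analysis. Nowhere does the article say that each channel is tested separately, that oxy- and deoxyhaemoglobin are both tested, that both visits are confirmatory, or that one significant channel would count as success. The second primary is worded as an association, which could be a single test. A separate SAP may define regions of interest and an FDR correction, and a condensed article need not repeat them. A general 5% level is also compatible with adjusted P values.

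Most of this stands. A reader might infer that 160 or more tests are planned and that a positive fNIRS finding is almost certain by chance. The documents do not support that inference: it needs channel-wise testing that is not stated, and correlation that is not high. At ρ = 0.9 the figure for 160 tests is 24%.

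It is also true that requiring both primaries to succeed would remove the inflation, and that NRS is in practice the powered outcome. But the article does not state a both-must-succeed rule, and it does not rank NRS above fNIRS. Which outcomes are primary, and what counts as success on them, is core protocol content. On that, the article fixes two primaries and a flat threshold and stops. This part of the concern does not depend on how the channels are analysed.

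**Conclusion.** The point holds at the level of the primary outcomes. With two primaries, a flat 0.05 and no success rule, the familywise error is about 8% to 10% (ρ from 0.7 to 0) if either may support a claim. It is about 12% to 34% (ρ from 0.9 to 0) if the fNIRS primary is one summary per task at two visits and any of the eight may be used. The 160-test figures, 24% to over 99.9%, show how much depends on the choices left open; they do not describe what the article says will be done. All figures assume two-sided tests, true nulls and a common correlation that the documents do not give.

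**What to change.** Amend the outcome and analysis sections before any outcome data are examined:

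- **Stage 2.** Test NRS at T10, CT versus DT, first at 0.05. Test the fNIRS primary at 0.05 only if NRS succeeds, using one pre-named region, task and visit.
- **Stage 1.** Pre-name one fNIRS measure as the confirmatory comparison of KOA patients with healthy volunteers.
- **Everything else.** Report the remaining channel, task, chromophore and visit tests as exploratory, with FDR control. If an SAP already defines regions or an FDR step, refer to it and make the two documents agree.

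The cost is wording. The fixed sequence takes no power from the NRS test, whereas splitting alpha to 0.025 would lower it from 90% to about 84% under the t-test assumption above. The downside is that the confirmatory fNIRS claim is limited to the pre-named measure and, in stage 2, cannot be made unless NRS succeeds.

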### Outcome measures

Outcome measures will be measured according to Osteoarthritis Research Society International [31]. Baseline measurements will be performed in the first stage, and the second stage will be measured at baseline and 5 (T5) and 10 (T10) days after intervention. The timeline for the second stage is shown in Table 1.

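### The between-group NRS test ignores baseline and does not settle whether score or change is compared; the separate within-arm tests need descriptive-only status

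*Protocol article*

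**What the plan says.** All references are to the protocol article.

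- **Primary outcomes, item (1):** the NRS outcome is "The difference in knee pain before and after treatment".
- **Outcome measures:** "the second stage will be measured at baseline and 5 (T5) and 10 (T10) days after intervention". A baseline and two later values are therefore planned for each patient.
- **Statistical analysis, between arms:** "For the comparison between groups after the intervention, the independent samples t test will be used if the data follow a normal distribution"; otherwise a Mann-Whitney U test. No covariate is named.
- **Statistical analysis, within arms:** a paired t test before against after, or a Wilcoxon test when the data are not normal. These tests are not marked as descriptive.
- **Statistical analysis, general:** "Data analysis will use an intention-to-treat analysis strategy" and "P ≤ 0.05 will be significantly different".
- **Conclusion, third listed advantage:** speaks of comparing changes in NRS between the groups.
- **Sample size:** "With a yielding power of 90% and a significance level of 0.05", "the sample size is intended to consist of 30 participants in each group". The calculation rests on before-after NRS in the first 10 participants; no effect size, SD or correlation is printed.
- **Randomization:** simple 1:1 allocation, with no stratification on pain.

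**The concern.** The outcome is defined as a change. The only sentence on the randomised comparison gives its timing (after the intervention) but not its variable, and the only sentence that mentions before and after concerns comparisons inside an arm. Read literally, change is tested only within arms and the arms are compared on follow-up scores alone. Read with the Conclusion section, the arms are compared on change. These are different analyses with different precision, and neither adjusts for baseline by regression.

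Three things are at stake:

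1. **Precision.** Baseline pain usually predicts follow-up pain. A test that leaves it out, or simply subtracts it, has a larger standard error than one that adjusts for it.
2. **Interpretation.** Both arms receive the same education and drugs, and entry requires an NRS of at least 3. Drug effect, natural course and regression to the mean can therefore move both arms. A significant change in CT beside a non-significant one in DT would look like an effect of physical therapy without being one.
3. **A fixed target.** A normality check on the trial data decides whether means or ranks are compared, so the quantity tested is not settled in advance.

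**Working it through.** **Inputs.** From the article: 30 evaluable patients per arm, power 90%, alpha 0.05 (taken as two-sided; sidedness is not stated). Assumed, because the article gives no figure: correlation r between baseline and follow-up NRS of 0.3, 0.5 or 0.7, equal SDs at both times, and the true effects shown. The entry cut-off narrows the range of baseline scores and may push r towards the low end.

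**Step 1: the plan's own figure.** The 30 per arm cannot be reproduced, because no effect or SD is printed. Solving backwards with the noncentral t distribution (df = 58, noncentrality d × √(30/2)), 90% power needs d = 0.851. Here d is the true CT-DT difference divided by the SD of the follow-up NRS. If the 30 came from a paired calculation, the matching standardised change is dz = 0.612.

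**Step 2: variance of the estimated arm difference, relative to the follow-up-score t test.** ANCOVA: 1 − r². Change score: 2(1 − r).

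| r | ANCOVA | Change score | ANCOVA ÷ change score |
|---|---|---|---|
| 0.3 | 0.91 | 1.40 | 0.65 |
| 0.5 | 0.75 | 1.00 | 0.75 |
| 0.7 | 0.51 | 0.60 | 0.85 |

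ANCOVA has the smallest variance in every row, so the recommendation does not depend on which variable the t test was meant to use.

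**Step 3: power with 30 per arm.** Replace d by d/√(1 − r²) in the noncentral t formula. At r = 0.5, for example, 0.851/√0.75 = 0.983.

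| True d | Unadjusted | ANCOVA r = 0.3 | r = 0.5 | r = 0.7 |
|---|---|---|---|---|
| 0.851 | 90.0% | 92.5% | 96.3% | 99.5% |
| 0.6 | 62.8% | 66.8% | 75.1% | 89.2% |

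A simulation of 40,000 trials at d = 0.851 and r = 0.5 gave 89.8% unadjusted and 95.9% adjusted. To keep 90% power at d = 0.851, ANCOVA needs about 28, 23 or 16 per arm at the three correlations.

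**Step 4: chance imbalance.** For arms of 36, P(gap ≥ 0.5 points) = 2[1 − Φ(0.5/(SD × √(2/36)))]. This is 16% at an assumed SD of 1.5 and 29% at 2.0. In a follow-up-score comparison the expected carry-over is r × gap: 0.15, 0.25 or 0.35 points for a 0.5-point gap.

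**Step 5: within-arm tests.** Suppose both arms truly change by the same standardised amount dz. With p the power of the paired t test at n = 30, the chance that exactly one arm is significant is 2p(1 − p).

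| dz | p | Exactly one arm significant |
|---|---|---|
| 0.3 | 0.355 | 46% |
| 0.4 | 0.563 | 49% |
| 0.5 | 0.754 | 37% |
| 0.6 | 0.888 | 20% |
| 0.8 | 0.988 | 2% |

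A valid between-arm test would be falsely significant in 5% of such trials. At dz = 0.612 the figure is 2 × 0.9 × 0.1 = 18%.

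**The case against.** The strongest reply is that the planned comparison is sound. Under randomisation an unadjusted t test keeps its type I error, a between-group comparison is planned, and nowhere does the article say that efficacy will be concluded from within-arm results. If the trial is powered at 90%, adjustment adds between 2.5 and 9.5 points. A chance baseline gap passes only partly into the result and is small beside the 1.8-point clinically important difference that the article cites. The dz values with the worst discordance are also the least favourable ones; large changes almost remove it. All of this stands. It makes the point one of efficiency and clarity, not of validity.

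A reader might also infer more than the article supports:

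- *That the plan is a completer analysis contradicting its intention-to-treat claim.* The article gives no completers-only rule and no imputation rule, and a condensed article may leave missing data to the full protocol. A bare t test omits patients without the value unless one is imputed, so this is a risk and not a stated contradiction.
- *That T5 and T10 are tested separately.* The article does not say which visit or visits the tests use.
- *That the baseline is certainly discarded.* The outcome definition and the Conclusion section leave open that changes are compared between arms, which would use the baseline, though less efficiently.

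The objection does not remove the core. The article chose and printed its tests, so this is not detail left to an analysis plan.

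**Conclusion.** The point holds as a recommended improvement, not as a fatal error. The article leaves open whether score or change is compared between arms, names no baseline-adjusted analysis, and places within-arm tests beside the randomised comparison without limiting their role.

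The loss is modest if the true effect is as large as the sample size implies and r is low. It reaches 12 to 26 points of power at d = 0.6 with r = 0.5 to 0.7. The chance of a misleading within-arm contrast is substantial for small to moderate common changes and minor for large ones. These sizes rest on assumed values of r, d and dz. The ordering of the methods does not: under equal SDs, (1 − r²)/[2(1 − r)] = (1 + r)/2, which is below 1 for every r below 1.

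**What to change.** In the Statistical analysis section:

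1. Name one primary NRS analysis: the CT-DT difference at T10 with 95% CI, adjusted for baseline NRS. Obtain it from a mixed model over T5 and T10 (arm, visit, arm × visit, baseline NRS) or from ANCOVA at T10. The mixed model also keeps patients who have T5 but no T10. ANCOVA at T10 does not, and neither helps a patient with no follow-up value.
2. Align the wording in Primary outcomes and in the Conclusion with that contrast.
3. Drop the normality check as the switch between tests; give a rank-based or bootstrap analysis as sensitivity.
4. Report within-arm changes with confidence intervals, as description only.
5. Use the same approach for WOMAC and PCS. Do not apply it to the fNIRS outcomes defined as associations with pain severity, because an arm-by-visit model does not estimate an association.

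Cost: wording only. The data are already planned and SPSS 26 fits these models.

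### The non-normal branch for before-after comparisons names an independent-samples test (Wilcoxon rank sum) for paired data

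*Protocol article*

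**What the plan says.** The Statistical analysis section of the protocol article sets out two families of comparison, each with a normal and a non-normal branch.

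- **Between groups after the intervention:** an independent samples t test if normal; otherwise the Mann-Whitney U "rank sum test will be used if the data are nonnormally distributed".
- **Within a group, before versus after:** "For intragroup comparisons before and after the intervention, a paired t test will be used if the data follow a normal distribution"; otherwise "the Wilcoxon rank sum test will be used for data that are not normally distributed".

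The threshold is "P ≤ 0.05 will be significantly different". Under Outcome measures, "the second stage will be measured at baseline and 5 (T5) and 10 (T10) days after intervention", so each patient contributes repeated scores. The first primary outcome reads "The difference in knee pain before and after treatment, will be measured by the NRS". The Sample size section is also framed as a before-after comparison: "The sample size will be determined by comparing the NRS scores before and after treatment based on a preliminary study of the first 10 participants".

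**The concern.** Before and after scores from the same patient are paired, and the plan recognises this by choosing a paired t test for the normal case. The Wilcoxon rank sum test and the Mann-Whitney U test are one procedure under two names, valid for independent samples. The plan therefore gives the same unpaired test to two different designs. The paired rank test, the Wilcoxon signed-rank test, is named nowhere in the document.

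Run as written, the non-normal branch treats 30 patients measured twice as 60 unrelated people. A normality check would then decide not only between a mean-based and a rank-based test but also between a paired and an unpaired analysis. Real within-group changes on the NRS, WOMAC or PCS could be missed. The NRS takes whole-number values from 0 to 10 and entry requires a score of at least 3, so use of the non-normal branch is plausible, although the document has no data on the distribution of the differences.

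**Working it through.** The plan states no figure for this point, so there is none to reproduce. The check has three steps.

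**1. Match test to design.**

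| Comparison | Data | Normal branch | Non-normal branch as written | Rank test that fits |
|---|---|---|---|---|
| CT vs DT after intervention | independent | independent samples t | Mann-Whitney U | Mann-Whitney U |
| Before vs after within a group | paired | paired t | Wilcoxon rank sum (= Mann-Whitney U) | Wilcoxon signed-rank |

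Only the last row is mismatched.

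**2. Direction and rough size of the error.** Let both scores have standard deviation σ and within-patient correlation ρ. The variance of a before-after difference is 2σ²(1 − ρ). An unpaired test behaves as if it were 2σ². Its standard error is therefore too large by a factor 1/√(1 − ρ) when ρ > 0, and a nominal two-sided 5% test has a true level of about 2Φ(−1.96/√(1 − ρ)):

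- ρ = 0.3: 1.96/√0.7 = 2.34, level about 1.9%
- ρ = 0.5: 1.96/√0.5 = 2.77, level about 0.6%
- ρ = 0.7: 1.96/√0.3 = 3.58, level about 0.03%

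This is a normal approximation. At ρ = 0 the level is correct; at negative ρ it exceeds 5%.

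**3. Simulation.** Inputs from the document: 30 patients per group (Sample size) and a threshold of 0.05 (Statistical analysis; two-sided assumed, as the side is not stated). Assumed, because the document gives neither: the correlation and the size of the change.

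*Bivariate normal scores, n = 30, 4,000 runs.* Two ways of setting the change were used. The first holds the standardised paired effect at dz = 0.61, which gives about 90% power for a paired t test with 30 pairs. Since dz = shift/(σ√(2(1 − ρ))), the raw shift is then 0.61 × √1.4 = 0.72 SD at ρ = 0.3, 0.61 SD at ρ = 0.5 and 0.61 × √0.6 = 0.47 SD at ρ = 0.7. The second holds the raw shift at 0.61 SD throughout.

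| ρ | Type I error, rank sum | Power at dz = 0.61, rank sum vs signed-rank | Power at 0.61 SD shift, rank sum vs signed-rank |
|---|---|---|---|
| 0.3 | 2.4% | 79% vs 88% | 63% vs 76% |
| 0.5 | 0.7% | 66% vs 89% | 66% vs 88% |
| 0.7 | 0.08% | 37% vs 89% | 68% vs 98% |

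The two settings coincide at ρ = 0.5. The type I errors agree with step 2 within simulation and approximation error.

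*Skewed scores rounded to 0–10, n = 30, 4,000 runs, shift 0.75 points (0.5 SD).* This is closer to the branch in question.

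| Latent ρ | Type I error, rank sum | Type I error, signed-rank | Power, rank sum vs signed-rank |
|---|---|---|---|
| −0.3 | 8.0% | 4.8% | 59% vs 41% |
| 0 | 4.6% | 4.7% | 60% vs 50% |
| 0.3 | 2.3% | 4.5% | 62% vs 64% |
| 0.5 | 1.0% | 4.8% | 63% vs 76% |
| 0.7 | 0.2% | 4.5% | 66% vs 89% |

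The signed-rank test stays close to 5% at every correlation. The rank sum test does so only at zero correlation.

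**The case against.** The strongest reply is that this is a naming slip. The section uses two different names in adjacent sentences and sets the second beside a paired t test, so the authors may well have meant the paired Wilcoxon test and would select it in the software. That is plausible, and the P values are wrong only if the wording is followed. It does not remove the point: the text names a specific unsuitable test, and nothing elsewhere corrects it.

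The scope is also narrow. Only the non-normal within-group branch is touched. The randomised comparison of CT with DT names a suitable test, and within-group change does not estimate the treatment effect. With positive correlation the error is lost power, not false positives. All of this stands and limits the seriousness.

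The size of the loss depends on the assumptions. The drop to 37% at ρ = 0.7 arises partly because a fixed dz shrinks the raw shift as correlation rises. With a shift of 0.84 SD the gap is small: 91% vs 96%, 95% vs 99% and 97% vs 100% at correlations of 0.3, 0.5 and 0.7. In the skewed setting at ρ = 0.3 it is also small (62% vs 64%). The loss is therefore better read from the fixed-shift results, as a range. The distortion of the type I error does not depend on the shift.

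Finally, fNIRS data go to a separate MATLAB module whose tests are not named, so an effect on those outcomes cannot be claimed.

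**Conclusion.** The point holds. The plan names an independent-samples test for paired data, and the P values from that branch would be invalid if it were run as written. For assumed correlations of 0.3 to 0.7 with 30 patients, the true type I error is about 2% down to 0.2% or less, against a nominal 5%. At a fixed moderate shift (0.5 to 0.61 SD) the power lost ranges from 2 percentage points (skewed scores, ρ = 0.3) to 30 (normal scores, ρ = 0.7). For large changes the loss is small; at negative correlation the test would be anti-conservative.

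These sizes rest on correlations and shifts that the document does not give. The mismatch itself rests on no assumption. It matters because the first primary outcome is a before-after difference on the NRS, on which the sample size is also said to be based, and because patients are measured at three time points.

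**What to change.** In the Statistical analysis section, replace the Wilcoxon rank sum test with the Wilcoxon signed-rank test for within-group before-after comparisons, and keep the Mann-Whitney U test for independent groups only. State that normality for this choice is judged on the paired differences. Carry the same wording into any separate analysis plan, and confirm that the analysis program calls the paired procedure. The change is one term and one clarifying clause; it has no effect on conduct, data collection or sample size, and should be made before the data are analysed.
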